32^ Furthermore, prior trials have not focused exclusively on strong anticholinergics, which hold the highest binding affinity to cholinergic receptors and would provide the strongest test of the link between anticholinergic medication and adverse cognitive effects.^33
34^

Therefore, we designed and initiated the randomized clinical trial, “Reducing the Risk of Dementia through Deprescribing” (R2D2) to evaluate the impact of a pharmacist-based deprescribing intervention on important cognitive and safety outcomes. The primary aim for the R2D2 trial is to determine the efficacy of anticholinergic deprescribing on objectively measured cognition compared to usual care in community-dwelling older adults. The secondary aim is to examine the quality of life and safety profile of anticholinergic deprescribing compared to usual care.

Our conceptual model (Figure 1) holds that removal of offending anticholinergic agents will lead to increased cholinergic neurotransmission and preserved or improved cognitive function including memory, executive cognitive ability, and speed of processing. The enhancement in neural function and cognitive function produced by the intervention should result in a lower risk of cognitive impairment or delay in the time to ADRD. This trial will focus on proximal outcomes with future studies planned to evaluate the impact on disease outcomes (i.e., diagnosis of ADRD).

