## Methods

The R2D2 trial primary objective is to determine the efficacy of an anticholinergic deprescribing intervention on cognition compared to usual care in older adults using strong anticholinergics at baseline. The second objective is to examine the quality of life and safety profile of deprescribing compared to usual care. Third, the study intends to determine whether demographic (age, gender, race), genetic (APOE 4 status), or clinical characteristics (comorbidities, number of medications) moderate the effect of the deprescribing intervention.

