The study intervention proposes to reduce exposure to medications that are prescribed to manage symptoms of depression, anxiety, insomnia, and pain. We will use the Patient Reported Outcomes Measurement Information System (PROMIS) to capture the four patient safety outcomes. PROMIS was developed by the National Institute of Health. It is unique in its ability to standardize scores across diagnoses and symptoms, it possesses excellent reliability and validity, and it is inclusive of diverse population characteristics and backgrounds.^53^ The PROMIS profile-29 (www.nihpromis.org) includes brief scales for several domains; we will use four-item scales for depression, anxiety, and sleep disturbance (insomnia), and a 3-item pain intensity scale.^53^ These and other safety measures (see below) will be collected at baseline and months 6, 12, 18, and 24. Comprehensive scoring manuals are available for each measure with guidance for interpreting individual and composite scales. Each PROMIS raw score can be converted to a T-score where 50 represents the general population norm for that symptom and each 10-point deviation represents one standard deviation (SD) from the population norm.

We will use the 15-item Health Utility Index (HUI) to determine each participant’s health-related quality of life (HRQOL) at baseline and months 6, 12, 18, and 24.^54^ The HUI is a utility-based HRQOL instrument applied in patients with a wide range of medical conditions. It has eight attributes: vision, hearing, speech, ambulation, dexterity, emotion, cognitive function and pain. The individual health domain scores range from 0.00 (maximum impairment) to 1.00 (no impairment) and the multi-attribute (HUI) scores, a multiplicative function of individual attribute levels, range from 0.36 to 1.00 with anchors 0.00 = dead and 1.00 = perfect health.

To assess adverse events, two methods are planned: 1) a single-item question will be asked at each follow-up assessment to collect self-reported adverse events, and 2) acute care utilization, defined as emergency room or hospitalization recognized through our statewide health information exchange (Indiana Network for Patient Care). Both methods will be reviewed and summarized at each meeting of the DSMB.

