33^ in which the daily dose is divided by the minimum effective dose. Days of standardized exposure for each medication will be the sum of the standardized days of exposure in a time period that includes each medication for each patient. This exposure is defined analogously to the pack-years concept used to characterize exposure to cigarette smoking and is a cumulative measure reflecting both exposure intensity and duration. Total exposure will be compared between the two groups using mixed effects models with group (intervention and control) as the independent variable adjusting for significant baseline variables and random PCP effects. We will then use the mixed effect model with cognitive scores at 6, 12, 18, and 24 months as outcome variables described above with total anticholinergic exposure as an additional independent variable adjusting for baseline cognitive scores and PCP random effects. Attenuation of the intervention effect from the original model would indicate that the effect of intervention is mediated through the reduction in anticholinergic exposure. Comparisons of PROMIS scores and HUI will be conducted similarly to the models we described above for cognitive scores. Exploration of potential moderation effects from *APOE*, or participants’ characteristics will be conducted by including each of these variables and its interaction with the randomization group in the mixed effects models for the outcome measures. Significant interactions will indicate significantly different intervention effects in subgroups defined by *APOE*, or participants’ characteristics.

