Interim analyses will not be conducted to evaluate conditional power (futility) or efficacy, thus preserving the overall Type-I error probability regarding the efficacy of the intervention. Given the nature of an elderly study population, we expect study attrition in the form of participant death or withdrawal. Our proposed analysis plan using mixed effects models are robust under the missing at random (MAR) assumption that the probability for dropping out depends on participants’ characteristics and medical conditions. We will compare patients’ characteristics between the completers and non-completers to detect potential violation to the missing at random assumption. We will conduct sensitivity analyses to assess the potential impact of missing data using multiple imputation which allows the imputation of missing outcomes for those who drop out using data gathered from these patients at baseline and prior to drop-out. We will use SAS software version 9.4 (SAS Institute, Cary, North Carolina) or relevant updated versions for all analyses.

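### The safety aim is a comparison with usual care, but its stated between-arm comparisons stop at PROMIS and HUI, and those scores are projected past death

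*Protocol article*

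**What the plan says.** The aim is comparative in two places. The Background has "The secondary aim is to examine the quality of life and safety profile of anticholinergic deprescribing compared to usual care", and the opening of Methods has "The second objective is to examine the quality of life and safety profile of deprescribing compared to usual care".

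Measures then names the instruments. For symptoms: "We will use the Patient Reported Outcomes Measurement Information System (PROMIS) to capture the four patient safety outcomes". HUI is added for quality of life, with dead anchored at 0.00. Adverse events come by two routes: "a single-item question will be asked at each follow-up assessment to collect self-reported adverse events", and "acute care utilization, defined as emergency room or hospitalization recognized through our statewide health information exchange". The stated use of both is: "Both methods will be reviewed and summarized at each meeting of the DSMB".

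The Analysis Plan gives the comparison for this aim in one sentence: "Comparisons of PROMIS scores and HUI will be conducted similarly to the models we described above for cognitive scores". Sample Size and Rationale gives precision for PROMIS and HUI only. The secondary outcomes in the Abstract are the PROMIS symptoms and quality of life. Table 1 has no row for adverse events, acute-care use or death.

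Death enters the Analysis Plan only in the missing-data paragraph: "we expect study attrition in the form of participant death or withdrawal". That paragraph assumes missingness at random and adds multiple imputation as a sensitivity analysis, using data from baseline and before drop-out. It makes no separate provision for participants who die.

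**The concern.** An aim worded as a safety comparison needs its main safety events in a between-arm analysis. Emergency visits and hospitalizations are collected, but the article assigns them to monitoring. Monitoring by a DSMB during the trial does not answer the aim at its end.

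Death is the sharper problem. A participant who has died cannot answer the self-report item, and a death outside acute care is not an event under the second method. The only stated handling of death is as missing data. A missing-at-random model, or an imputation built from earlier scores, then supplies the score that the person would have had if alive. For HUI this conflicts with the scale's own anchor. If the arms differed in deaths or hospital use, the stated comparisons could still look neutral.

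**Working it through.** **1. The plan's own figures for this aim.** Inputs from Sample Size and Rationale: effective n = 96 per group, intraclass correlation 0.05, 6 patients per physician, 30% attrition, half-width 0.3 SD, stated probability 85.6%.
- Design effect: 1 + (6 − 1) × 0.05 = 1.25. 96 × 1.25 = 120, as stated.
- Attrition: 120 / 0.70 = 171.4, rounded up to 172, as stated.
- Precision: P(t × S × √(2/96) ≤ 0.3), with t the 0.975 quantile on 190 df and SD = 1. The half-width at S = 1 is 0.285 SD, and the probability is 85.8% against 85.6% stated.

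These figures reproduce. The problem lies in which outcomes they cover.

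**2. Where each safety quantity appears.**

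| Quantity | Collected (Measures) | Between-arm model (Analysis Plan) | Precision (Sample Size) | Table 1 |
|---|---|---|---|---|
| PROMIS scales | yes | yes | yes | yes |
| HUI | yes | yes | yes | yes |
| Self-reported adverse events | yes | not stated | not stated | no row |
| Emergency visit or hospitalization | yes | not stated | not stated | no row |
| Death | in neither method's definition | as attrition only | not stated | no row |

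**3. What projection past death does to HUI.** The article prints a range of 0.36 to 1.00 for the multi-attribute score, with dead at 0.00. A dead participant given a score in that range instead of 0.00 is overvalued by 0.36 to 1.00. Each percentage point of difference in mortality between arms would then hide 0.01 × 0.36 = 0.0036 to 0.01 × 1.00 = 0.0100 in the mean HUI difference. The article gives no mortality figure, so the total cannot be stated.

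**4. What a by-arm acute-care estimate would deliver.** The article gives no event rate, so 20% to 50% of participants with at least one event in 24 months is assumed. The 1.25 design effect is carried over, also an assumption, because the article bases its intraclass correlation on prescribing patterns. Effective n = 172 / 1.25 = 137.6 per arm. Half-width = 1.96 × √(2p(1 − p)/137.6).
- p = 0.20: 9.5 points
- p = 0.30: 10.8 points
- p = 0.40: 11.6 points
- p = 0.50: 11.8 points

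The increase detectable with 80% power is about 15 to 17 points.

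**5. Death.** Expected drop-outs: 344 − 240 = 104. The article does not divide these into deaths and withdrawals. If 10% to 30% were deaths, that is 10 to 31 deaths, or 3% to 9% of 344. At risks of 3% to 9% the half-width is about 4 to 7 points, and power to detect a doubling is 22% to 59%.

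**The case against.** The strongest reply is that this is a condensed article. Tables of adverse events, utilization and deaths by arm commonly sit in a full protocol or SAP that is not shown. The DSMB sentence does not say that monitoring is the sole use. That stands: a reader might infer that these data will never be compared between arms, and the document does not support that. What it supports is that no other use is stated, in an article that does spell out the comparison and the precision for this same aim.

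It can also be said that recurrence of depression, anxiety, insomnia and pain is the natural safety endpoint when drugs for those symptoms are withdrawn, with events left to an external board. As a choice of inferential endpoint this is coherent. It does not settle how death is handled.

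Two stronger readings are tempting. One is that safety would be judged from survivors' symptom scores alone, with the worst-off participants dropped. This is wrong: HUI is compared too, the analysis is by intention to treat, and the mixed models use every score recorded before death or withdrawal. The other is that only 240 of 344 participants would contribute PROMIS or HUI data. The 240 is the number needed to complete the trial; participants with partial follow-up also contribute.

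Finally, multiple imputation is only a sensitivity analysis, completers are compared with non-completers, and quoting an anchor does not oblige a trial to score deaths at zero. All true. But comparing characteristics of completers and non-completers is not a comparison of deaths by arm, and the primary model makes the same projection under missingness at random.

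**Conclusion.** The point holds in a limited form. The stated between-arm comparisons for a comparative safety aim cover PROMIS and HUI only. Acute-care use and adverse events have DSMB summary as their only stated use, and neither method is defined to record death. The firmest part does not depend on silence: the missing-data paragraph puts death together with withdrawal and makes no exception for it, so scores are projected past death on a scale that the article anchors at 0.00 for dead.

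The direction and size of any effect on the results are unknown, since the article gives no mortality or event rates. The half-widths of about 9 to 12 points for acute-care use and 4 to 7 points for death rest on assumed risks and on the 1.25 design effect applying to these outcomes. They describe what an added analysis could deliver and are not an error in the plan's arithmetic. The change should be made, and the SAP should be checked first in case it already covers part of it.

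**What to change.** **Missing-data paragraph of the Analysis Plan.** Separate death from withdrawal. State that PROMIS, HUI and cognitive scores are not imputed after death. Add a supportive HUI analysis that scores death as 0.00 at the visits after it. Because the mixed model still projects implicitly, this supportive analysis is what shows whether the HUI conclusion depends on it.

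**Comparison section of the Analysis Plan, and Table 1.** Add emergency visit or hospitalization through 24 months, and all-cause death, as descriptive safety outcomes by assigned arm. Give each an estimate and a 95% confidence interval that allows for clustering by primary care physician. Use exchange data for all randomised participants as far as their authorization allows, and whatever death information the trial already obtains. The article does not say that the exchange holds dates of death, or that consent covers passive follow-up after telephone assessments stop; confirm both before the wording is fixed.

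**Cost.** Wording, two rows in Table 1, and a few cluster-adjusted estimates; the acute-care data are already being obtained. The estimates will be imprecise, and power for death will be low, so they should be presented as estimates with intervals and not as tests.

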### Data Management

Study data are collected and managed using the Research Electronic Data Capture (REDCap) electronic data capture tools supported by the Clinical and Translational Sciences Institute at Indiana University.^56
57^ REDCap is a secure, web-based software platform designed to support data capture for research studies, providing 1) an intuitive interface for validated data capture; 2) audit trails for tracking data manipulation and export procedures (auditing is independent of investigators and sponsors); 3) automated export procedures for seamless data downloads to common statistical packages; and 4) procedures for data integration and interoperability with external sources.

### Analysis Plan

The cluster randomized trial design will be used by randomizing primary care physicians (PCP) into the intervention or usual care arms. Outcomes will be collected and analyzed at the patient level. We will examine assigned randomization against the computer-generated randomization scheme to ensure randomization validity. Patient characteristics between the two groups will be compared using mixed effects models for continuous variables and generalized estimating equations for categorical variables while adjusting for random PCP effects. We will examine the distributions of continuous variables and use alternative approaches such as transformation or nonparametric methods in cases of violation to the normal distribution assumption. We will also examine the frequency distribution of all categorical variables and adopt exact inference procedures in cases of zero or small cell size. Any baseline variable that is found to be significantly different between the two groups will be included as a covariate in the analyses outlined below.

An intension to treat approach will be used in the analysis of all outcome measures. Composite cognitive scores collected at 6, 12, 18 and 24 months will be used as the primary outcome variables in mixed effects models. An indicator variable for intervention group (intervention vs usual care), time, interaction between group and time, and baseline cognitive scores will be included as independent variables as well as significant factors from the baseline comparison. PCP will be used as random effects to adjust for within-physician correlations. Significant group and time interaction or significant group main effect will indicate differences in cognitive function between the two groups. If significant interactions between group and time are found, post-hoc analyses will be conducted to determine the times when the two groups have significantly different cognitive scores. A significant main group effect in the absence of a group-by-time interaction would indicate differences between groups in cognitive function at all follow-up time points.

In a second set of models, we will determine whether differences between groups were accounted for by decreases in total exposure to anticholinergics from baseline to 24 months. For each medication, standardized daily exposure will be calculated using standardized daily dose as in the study by Gray^7^ and validated in our prior work^14
17
33^ in which the daily dose is divided by the minimum effective dose. Days of standardized exposure for each medication will be the sum of the standardized days of exposure in a time period that includes each medication for each patient. This exposure is defined analogously to the pack-years concept used to characterize exposure to cigarette smoking and is a cumulative measure reflecting both exposure intensity and duration. Total exposure will be compared between the two groups using mixed effects models with group (intervention and control) as the independent variable adjusting for significant baseline variables and random PCP effects. We will then use the mixed effect model with cognitive scores at 6, 12, 18, and 24 months as outcome variables described above with total anticholinergic exposure as an additional independent variable adjusting for baseline cognitive scores and PCP random effects. Attenuation of the intervention effect from the original model would indicate that the effect of intervention is mediated through the reduction in anticholinergic exposure. Comparisons of PROMIS scores and HUI will be conducted similarly to the models we described above for cognitive scores. Exploration of potential moderation effects from *APOE*, or participants’ characteristics will be conducted by including each of these variables and its interaction with the randomization group in the mixed effects models for the outcome measures. Significant interactions will indicate significantly different intervention effects in subgroups defined by *APOE*, or participants’ characteristics.

Interim analyses will not be conducted to evaluate conditional power (futility) or efficacy, thus preserving the overall Type-I error probability regarding the efficacy of the intervention. Given the nature of an elderly study population, we expect study attrition in the form of participant death or withdrawal. Our proposed analysis plan using mixed effects models are robust under the missing at random (MAR) assumption that the probability for dropping out depends on participants’ characteristics and medical conditions. We will compare patients’ characteristics between the completers and non-completers to detect potential violation to the missing at random assumption. We will conduct sensitivity analyses to assess the potential impact of missing data using multiple imputation which allows the imputation of missing outcomes for those who drop out using data gathered from these patients at baseline and prior to drop-out. We will use SAS software version 9.4 (SAS Institute, Cary, North Carolina) or relevant updated versions for all analyses.

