### Randomization procedures

In this cluster randomized trial, randomization occurs at the level of primary care provider in a 1:1 proportion between intervention and usual care using a randomization list with a computer-generated random scheme in random blocks of 4 or 6 stratified by healthcare system. Research staff are blinded to provider allocation status at the time of recruitment and throughout the study to avoid bias in data collection.

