The presence of APOE 4 alleles may modify the effect of anticholinergics on cognitive impairment, therefore, we originally planned to collect blood from each participant at baseline to include as a covariate in the responder analysis (secondary aim). However, given the COVID-19 interruption of in-person research, we revised our procedures to collect the APOE 4 variable remotely through saliva samples. Genomic DNA will be extracted from saliva samples using the DNeasy Blood & Tissue Kit (Qiagen, Inc., Valencia, CA) according to the manufacturer’s protocol. Sample kits will be distributed by mail to participant homes with instructions on how to complete and with pre-paid packaging to return to the Indiana Biobank for storage and processing. The sample kit will be distributed at the beginning of the study, but may be completed at any time of participation, and must be completed before 24 months or withdrawal from the study. Extracted DNA will be sent to LGC Limited, the preferred genotyping resource of the Indiana Alzheimer’s Disease Center and the Indiana Clinical and Translational Sciences Institute.

Because individual differences have potential to modify treatment outcomes, we will measure the following demographic and clinical factors: age, self-reported race, self-reported gender, self-reported years of education, and relevant clinical diagnoses impacting cognition such as depression, cardiovascular disease, stroke, and diabetes as we have done in prior studies.^8
17
55^ These demographic variables will be collected at baseline while diagnoses from the electronic medical record will be collected at baseline and 24 months (see Table 1). We will collect medication use through both self-report at baseline and each outcome assessment, and extract prescribed medications (medication orders) from electronic medical records prior to enrollment as well as during the 24-month study period.

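### Covariates beyond the baseline cognitive score enter the primary model only if they differ significantly between arms, a criterion that does not measure prognostic value

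*Protocol article*

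**What the plan says.** The Analysis Plan first sets up between-arm tests at baseline, adjusted for physician: "Patient characteristics between the two groups will be compared using mixed effects models for continuous variables and generalized estimating equations for categorical variables". It then turns the results into a selection rule: "Any baseline variable that is found to be significantly different between the two groups will be included as a covariate". It gives neither a candidate list nor a significance level for this screening.

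The rule applies to the primary analysis. Besides group, time and their interaction, the mixed model for the cognitive composite is specified so that "baseline cognitive scores will be included as independent variables as well as significant factors from the baseline comparison", with physician as a random effect. The same rule governs the comparison of total anticholinergic exposure, and the PROMIS and HUI comparisons follow the same modelling approach.

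Elsewhere the article names variables that it regards as relevant to outcome. Measures lists "age, self-reported race, self-reported gender, self-reported years of education, and relevant clinical diagnoses impacting cognition such as depression, cardiovascular disease, stroke, and diabetes". The Methods introduction adds possible moderators: "genetic (APOE 4 status), or clinical characteristics (comorbidities, number of medications) moderate the effect". Randomization procedures describes allocation in "random blocks of 4 or 6 stratified by healthcare system". None of these, healthcare system included, is a fixed term of the primary model.

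**The concern.** A covariate sharpens the treatment estimate when it predicts the outcome. A significance test of baseline balance measures something else: how far the arms happen to differ on that variable. A strong predictor of cognition can be moderately imbalanced without reaching significance and stay out, while a variable unrelated to cognition can enter by chance.

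Two things are at stake. The content of the primary model is unknown until the randomised arms have been compared, so the primary analysis is not fully specified. And the precision available from predictors that are already being collected is given up whenever they look balanced, which under sound randomisation is most of the time.

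This is not a detail left to a statistical analysis plan. The article states a definite rule, and the rule uses the wrong criterion.

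**Working it through.** **The plan's own figures.** Sample Size and Rationale gives 96 per group before clustering, ICC 0.05, 6 patients per physician and 30% attrition.
- Design effect: 1 + (6 − 1) × 0.05 = 1.25.
- Completers: 96 × 1.25 = 120 per group.
- Enrolment: 120 / 0.7 = 171.4, rounded up to 172 per group, or 344 in total.

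These agree with the article. The starting 96 is taken as given; the point does not depend on it.

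**How often the rule selects by chance.** Assumptions: screening level 0.05 (not stated), independent tests, truly balanced variables. The chance that at least one of k variables enters is 1 − 0.95^k.
- k = 8 (the factors named in Measures): 1 − 0.95^8 = 33.7%.
- k = 11 (adding APOE 4, comorbidities and medication count): 1 − 0.95^11 = 43.1%.

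Any single balanced prognostic factor is left out with probability 1 − 0.05 = 95%.

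**What this does to error rate and power.** A simulation used 20 physicians per arm with 6 completers each, ICC 0.05 treated as known, eight covariates, a single outcome and 3,000 runs per scenario. R² is the share of outcome variance that the eight covariates explain together. At least one covariate was selected in 29–31% of runs.

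| R² | Type I error, rule | Type I error, all prespecified | Power at 0.4 SD, no covariates | Power, rule | Power, all prespecified |
|---|---|---|---|---|---|
| 0.1 | 4.6% | 5.1% | 77.9% | 78.0% | 81.8% |
| 0.2 | 4.4% | 4.3% | 76.5% | 77.4% | 83.9% |
| 0.3 | 4.3% | 4.9% | 77.1% | 78.3% | 88.9% |

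Mean estimates under the rule were within 0.004 SD of the true value (0 or 0.4). The rule behaves almost like no covariate adjustment.

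**A realistic size.** The article gives no R². It must be read as variance explained beyond baseline cognition, which is always in the model. The plan's own correlations limit it. Outcomes 18 months apart are assumed to correlate at 0.1, and a time-constant predictor with a constant effect adds its full R² to that correlation. Unless the remaining correlation is negative, R² cannot exceed about 0.1. A range of 0.05–0.10 is therefore used.

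*Gain in effective sample size:*
- Covariates reduce all variance components, 1/(1 − R²): 1/0.95 = 1.053 and 1/0.90 = 1.111.
- Covariates reduce only within-physician variance. The design effect splits into 6 × 0.05 = 0.30 between physicians and 0.95 within. The gain is 1.25/(0.30 + 0.95 × 0.95) = 1.040 and 1.25/(0.30 + 0.95 × 0.90) = 1.082.

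Together this is roughly 4–11%.

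*Power, starting from 80% (two-sided 0.05 assumed):* Φ(2.802 × √gain − 1.960).
- Gains of 1.053 and 1.111 give 82.0% and 84.0%.
- Gains of 1.040 and 1.082 give 81.5% and 83.0%.

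That is about 2–4 percentage points.

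**The case against.** The strongest defence is that the most important covariate is safe. The baseline cognitive score is in the model whatever the balance, so a reader who infers that the plan drops all known prognostic factors would be wrong. This stands, and it is why the gain is counted only beyond baseline cognition.

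A reader might also infer that choosing covariates by a preliminary test biases the estimate or inflates the type I error. Neither is supported. The rule is stated in advance and uses baseline data only, so it offers no route to picking covariates by their effect on the result. The simulated type I error was 4.3–4.6%, with no visible bias. A chance entrant that is unrelated to cognition costs little.

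It is tempting to claim a larger loss, for instance by taking R² of 20% or more. The article gives no such value, and its own planning correlations point to about 10% or less.

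The number of physicians is not stated either. It is about 57 if 344 is divided by 6, but 40 if the 240 completers are, so no argument here rests on it.

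Finally, baseline comparisons have a legitimate use in this design. Providers may opt out or exclude patients, and the wording on blinding of staff at recruitment implies that allocation can precede patient enrolment. A comparison of arms can reveal recruitment imbalance. This stands as a reason to keep the comparisons, but not to let them choose the covariates.

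**Conclusion.** The point holds as a question of model specification and precision. The rule selects on a criterion unrelated to prognostic value. It adds at least one truly balanced variable by chance about 34% of the time with eight candidates and 43% with eleven, and omits each balanced prognostic factor about 95% of the time. These figures assume independent tests at 0.05. The randomisation stratum is not guaranteed a place in the model.

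The precision forgone is modest: roughly 4–11% of effective sample size, or about 2–4 percentage points of power, if the extra covariates explain 5–10% of variance beyond baseline cognition. That share is an assumption. The trial's validity is not in doubt on this ground. The change is worth making because it settles the primary model in advance and costs almost nothing.

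**What to change.** Delete the significance rule for choosing covariates, both where it is introduced and where it enters the primary, exposure, PROMIS and HUI models. Before outcomes are compared by arm, fix the covariates of the primary model as:
- the baseline cognitive composite;
- healthcare system;
- age;
- years of education.

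Add others only if they are named in advance for expected prognostic value. Keep all of them whatever the observed balance. Use the corresponding baseline score in the PROMIS and HUI models.

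Baseline comparisons may stay as a check on recruitment imbalance. Any adjustment prompted by an observed difference becomes a labelled sensitivity analysis.

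The cost is one paragraph of wording and a few degrees of freedom. The variables are already collected and the planned sample size does not change. The article plans no interim efficacy analysis and expects data collection to run to July 2026, so on the article's own timetable there is time to make the change before outcomes are compared by arm.
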